## Abstract

**Background:**

Standard therapy for borderline-resectable pancreatic cancer in the UK is surgery with adjuvant chemotherapy, but rates of resection with clear margins are unsatisfactory and overall survival remains poor. Meta-analysis of single-arm studies shows the potential of neo-adjuvant chemo-radiotherapy but the relative radio-resistance of pancreatic cancer means the efficacy of conventional dose schedules is limited. Stereotactic radiotherapy achieves sufficient accuracy and precision to enable pre-operative margin-intensive dose escalation with the goal of increasing rates of clear resection margins and local disease control.

**Methods/Design:**

SPARC is a “rolling-six” design single-arm study to establish the maximum tolerated dose for margin-intensive stereotactic radiotherapy before resection of pancreatic cancer at high risk of positive resection margins. Eligible patients will have histologically or cytologically proven pancreatic cancer defined as borderline-resectable per National Comprehensive Cancer Network criteria or operable tumour in contact with vessels increasing the risk of positive margin. Up to 24 patients will be recruited from up to 5 treating centres and a ‘rolling-six’ design is utilised to minimise delays and facilitate ongoing recruitment during dose-escalation. Radiotherapy will be delivered in 5 daily fractions and surgery, if appropriate, will take place 5–6 weeks after radiotherapy. The margin-intense radiotherapy concept includes a systematic method to define the target volume for a simultaneous integrated boost in the region of tumour-vessel infiltration, and up to 4 radiotherapy dose levels will be investigated. Maximum tolerated dose is defined as the highest dose at which no more than 1 of 6 patients or 0 of 3 patients experience a dose limiting toxicity. Secondary endpoints include resection rate, resection margin status, response rate, overall survival and progression free survival at 12 and 24 months. Translational work will involve exploratory analyses of the cytological and humoral immunological responses to stereotactic radiotherapy in pancreatic cancer. Radiotherapy quality assurance of target definition and radiotherapy planning is enforced with pre-trial test cases and on-trial review. Recruitment began in April 2015.

**Discussion:**

This prospective multi-centre study aims to establish the maximum tolerated dose of pre-operative margin-intensified stereotactic radiotherapy in pancreatic cancer at high risk of positive resection margins with a view to subsequent definitive comparison with other neoadjuvant treatment options.

**Trial registration:**

ISRCTN14138956. Funded by CRUK

## Background

Pancreatic cancer is responsible for only 3 % of cancer diagnoses but 5 % of cancer deaths, making it the fifth leading cause of cancer death in the UK (9408 cases in 2013 and 8817 deaths in 2014) [1]. Radical surgical resection represents the only chance of long-term disease control, but was possible for just 8 % of UK patients diagnosed in 2006–2010 [2]. In Europe standard practice for resectable disease is surgery followed by chemotherapy, but for these patients median survival is only 24 months and 50 % of patients will suffer local recurrence [3] suggesting that further improvement in multi‐modal therapy is required.

The failure to consistently achieve microscopic surgical clearance contributes to the high rates of disease relapse: alongside tumour size, grade and lymph node metastases, resection margin involvement has been repeatedly shown to predict long-term survival [4–6]. Accurate margin assessment requires comprehensive examination of the surgical specimen and rates of margin involvement are higher when a standardised protocol is used [7]. Despite centralization of services and improvement in diagnostic radiology, positive margins were reported in >35 % of patients in the largest multi‐national adjuvant trial in pancreatic cancer involving over 1000 patients (ESPAC 3), which again reinforced that patients with positive margins have poor outcome (hazard ratio 1.35, 95 % confidence interval 1.17‐1.56, *p* < 0.001) [8].

A small proportion of patients present with pancreatic tumours that can be classified as “borderline-resectable”, defined by a limited extent of vascular invasion. For these patients resection is possible but is likely to require vascular reconstruction and there is an especially high risk of positive resection margins, reported to be 62.9 % in the UK [9]. The concept of Borderline Resectable Pancreatic Cancer (BRPC) was initially described in 2001 by Mehta et al., describing 15 cases initially assessed as “marginally resectable” but where resectability was improved with preoperative chemo-radiotherapy [10]. The definition of BRPC was refined by an AHPBA/SSO/SSAT consensus statement [11, 12], now adopted by the NCCN [13]:-Venous involvement of the SMV or PV with distortion or narrowing of the vein or occlusion of the vein with suitable vessel proximal and distal, allowing safe resection and reconstructionGastro‐duodenal artery encasement up to hepatic artery with either short segment encasement or direct abutment of the hepatic artery, without extension to the celiac axisTumour abutment of the SMA not to exceed greater than 180° of the circumference of the vessel wall.

An alternative definition of BRPC by the MDACC has not been as widely recognised [14]. A multidisciplinary team approach is needed to assess the likelihood of attaining negative margins and this should remain the key consideration in determining if a patient is a potential candidate for resection [14, 15].

The management of BPRC is controversial, and there is increased interest in pre-operative treatment strategies that may improve outcomes [16]. Theoretical advantages include a greater chance of delivering full dose treatment, while drawbacks include possible over-treatment of resectable disease, the need for a biopsy and stent to relieve obstruction while awaiting surgery. Many patients presenting with localised disease develop frank metastases shortly after diagnosis and if this occurs during induction therapy these patients can be spared inappropriate and futile surgery [14].

Pre-operative (chemo) radiotherapy aims to treat the tumour in situ to achieve tumour regression and facilitate curative resection. This approach has become standard of care for some tumour sites, having been shown to reduce local recurrence in rectal cancer [17], and increase overall survival in oesophageal cancer [18], but is not established in pancreatic cancer due to limited effectiveness of standard dose schedules, despite potential advantages over postoperative treatment [19]. A complete tumour response is only seen in around 5 % of patients [20], though a larger proportion of patients (35 %) benefit from tumour down-staging to achieve resectability [21] and patients who successfully complete neoadjuvant chemoradiotherapy and go on to have resection tend to have high rates of clear resection margins [22, 23] and reduced rates of local recurrence [24, 25].

Stereotactic body radiation therapy (SBRT) combines rigorous immobilisation and image-guidance with hypofractionation, to reduce radiotherapy planning margins and treat small targeted volumes with greater accuracy and precision, supporting safe delivery of much higher biologically effective doses. It has been shown to be a highly-effective local treatment option in unresectable pancreatic cancer with high rates of local control achieved using treatment delivered in a single exposure [26–29], and when treatment was delivered in 3–5 fractions lower rates of toxicity were seen without compromising disease control [30–35].

The specific goal in treating BRPC with pre-operative radiotherapy will be improve the chances of achieving clear resection margins, reduce risk of local recurrence and achieve chances of long-term survival similar to those for patients with initially resectable tumours. Neoadjuvant treatment has been shown to be deliverable and effective in BRPC, such as in a series of 160 patients described by Katz et al., among whom 78 % completed preoperative therapy and restaging, and 41 % underwent pancreatectomy, with a 94 % rate of clear margins [36].

The premise of the SPARC trial is a Margin-Intense radiotherapy concept where the whole tumour is treated to a minimum dose while a simultaneous integrated boost (SIB) is used to deliver additional dose to the margin of tumour around structures such as the superior mesenteric artery (SMA), SMV or portal vein and retroperitoneal margin. This approach complements surgery as these are the most difficult margins to resect and are at highest risk of positive surgical margins. Prospective dose-escalation aims to establish the maximum tolerated dose for this treatment paradigm for subsequent definitive investigation of efficacy. Once the maximum tolerated dose (MTD) is established this will provide a platform to integrate with optimal systemic treatment.

## Methods/Design

### Study design

The SPARC trial is a phase I dose-escalation study using the rolling six design [37] to establish MTD of SBRT delivered in the pre-operative setting for borderline resectable pancreatic cancers. This method minimises delays in the dose escalation phase [37]. Patients will complete SBRT in approximately one week and surgery will take place 5–6 weeks after radiotherapy. Patients will be on the study for 36 weeks from registration to end of treatment visit followed by standard care for two years post SBRT day one for the last patient, or when all participants have died.

The trial opened in April 2015 and will recruit up to 24 patients from five UK centres (Oxford, Glasgow, Leeds, Newcastle and Nottingham). The SPARC trial is conducted in accordance with the Helsinki Declaration (1996) and the regulatory requirements for clinical trials of an investigational medicinal product under the European Union Clinical Trials Directive. The trial is approved by the National Research Ethics Service Committee South Central – Oxford B (REC reference: 15/SC/0059) and is sponsored by the University of Oxford, with funding from Cancer Research UK. Data submission for the SPARC trial is via electronic submission into the online database system OpenClinica by site staff. The Oncology Clinical Trial Office (OCTO) coordinates and manages the trial while the Centre for Statistics in Medicine (University of Oxford) will perform all statistical analysis.

### Participants

The inclusion and exclusion criteria for the SPARC trial are summarised in Table 1.

**Table 1 Tab1:** SPARC Inclusion/Exclusion criteria

Inclusion criteria	Exclusion criteria
1. Borderline resectable localised tumour of the pancreatic head/uncinate process/body as per NCCN Guidelines (tumours of the tail of pancreas are not eligible for inclusion) or operable tumour in contact with vessels increasing the risk of positive margin as defined by CT +/− MRI +/− PET criteria within 28 +/− 7 days prior to trial entry, de novo or following systemic treatment. 2. Histologically proven pancreatic ductal adenocarcinoma or cytological proven pancreatic malignancy 3. Able to undergo biliary drainage using a stent 4. Deemed fit and suitable for surgical resection. 5. No overt metastases or uncertain status with investigations suspicious of possible metastatic disease (e.g., small equivocal pulmonary nodule(s)). 6. Male or female, Age ≥16 years 7. Life expectancy of at least 6 months 8. ECOG performance status 0–1 9. The patient is willing and able to comply with the protocol for the duration of the study, and scheduled follow-up visits and examinations 10. Written (signed and dated) informed consent and be capable of co-operating with protocol 11. Haematological and biochemical indices within specified ranges.	1. Definitive metastatic disease or local disease that cannot be encompassed in the SBRT field. 2. History of previous or concurrent malignancy diagnoses for which the expected prognosis is likely to be worse than that of the current diagnosis of pancreatic cancer (excludes for example: e.g., localised prostate cancer, early colorectal cancer, early breast cancer, curatively-treated basal cell carcinoma of skin, carcinoma in situ of cervix; curatively treated cancer of other sites who are recurrence free for >3 years). 3. Serious medical or psychological condition precluding trial intervention. 4. Previous upper abdominal or right chest wall radiotherapy where 30 % of the liver has received >15Gy. 5. Pregnancy: Pregnant or breast-feeding women are ineligible. Women of childbearing potential must use effective methods of contraception. 6. Any other psychological, social or medical condition, physical examination finding or laboratory abnormality that the Investigator considers makes the patient a poor trial candidate or could interfere with protocol compliance or the interpretation of the trial results.

### Interventions

At registration patients are assigned to the appropriate SBRT dose level (Table 2) and will receive 5 fractions of SBRT over 5–8 days. The dose schedules selected have been designed to achieve approximately equivalent dose to the tumour to that used in conventionally fractionated radical radiotherapy (50-66Gy in 2Gy fractions) while the dose selected for the ‘at risk volume’ (area at risk of positive margin) is higher, to achieve increased likelihood of ablation of tumour cells. A maximum of 4 dose levels (including one de-escalated dose level) are expected to be needed to establish the MTD.

**Table 2 Tab2:** Radiotherapy dose escalation levels

Radiotherapy dose level	Tumour (PTV)				Area at risk of R1 (PTV_R)			
	Dose/# [Gy]	Total dose [Gy]	*BED [Gy_10_]	EQD_2_ [Gy]	Dose/# [Gy]	Total dose [Gy]	*BED [Gy_10_]	EQD_2_ [Gy]
Level −1	6	30	50	40	8	40	72	60
Level 1	6	30	50	40	9	45	88	71.5
Level 2	6.5	32.5	56	45	9.5	47.5	92	77.2
Level 3	7	35	62	50	10	50	100	83.3

**BED [Gy*
_*10*_
*]* biologically effective dose for acute reacting tissues (α/β = 10), *EQD*
_*2*_ equivalent dose in 2-Gy fractions

Dose level assignment will be based on the number of dose limiting toxicities (DLTs) observed, and the number of patients have no DLTs yet, but are still in the DLT assessment period as defined in the outcome measure below (i.e., toxicity data pending/evaluable not yet). In this trial design, the first two patients are treated at level 1. The third patient will be treated at level −1 if two DLTs have been observed. If at least one patients enrolled is not evaluable yet and less than 2 DLTs have been observed, this third patient will be entered at the same dose level, Level 1. For the fourth patient, if toxicity data is pending for at least one of the patients enrolled, the fourth patient will be allocated to the same dose level. But, if there are two or more DLTs when the fourth patient enters the study, the dose level will be de-escalated. The dose level will be escalated if there is no DLT after the first three patients finish the DLT assessment period. This process will be repeated for patients five and six. After the sixth patient is enrolled to a dose cohort, accrual will be only temporarily suspended until toxicity data is fully available for these six patients and/or a decision from the Trial Management Group (TMG) is made. Recruitment will stop once the MTD is identified.

### Outcome measures and definitions

The primary endpoint of the SPARC study is MTD, defined as the highest level of SBRT at which no more than 1 of 6 patients or 0 of 3 patients experiences a DLT in the period from starting SBRT to one month post-surgery or one month after the evaluation in week 3 post-SBRT if no surgery takes place. DLT is defined as these possible adverse events (AEs) (according to CTCAE v4.03), seen in the DLT assessment period:≥ Grade 3 upper gastro-intestinal (GI) bleeding≥ Grade 4 nausea/vomiting uncontrolled after 48 h of standard treatment≥ Grade 4 pancreatitis not stent relatedInterruption of SBRT >1 week due to SBRT-related AEs≥ Grade 4 vascular events: SMV thrombosis, bowel ischaemia due to SMA arteritis/stenosis, friable vessels at surgeryOther AEs that the TMG agrees to be dose limiting and possibly related to SBRT such as ≥ grade 3 gastrointestinal fistula >30 days after surgery

Secondary outcomes include resection rate, resection margin status rates, rate of pathological complete response, late SBRT toxicity, efficacy and long term safety. Resection rate is defined as the proportion of patients with radical oncological resection of pancreatic cancer over the total enrolled patients. Resection margin status (R0/R1/R2) is defined according to the standards of the Royal College of Pathologists, and response rate is defined as the rate of patients with pathological complete response over the total enrolled patients. Late toxicity is defined as any GI AE/other AE > grade 2 occurring between 1 month and 6 month post-surgery. Additional secondary outcomes include efficacy and long term safety as indicated by progression free survival (PFS) and overall survival (OS). PFS is defined as the time from date of first SBRT dose to the first date of progression or death for any cause, or is censored at the date of last known follow-up date if they are not observed to die during the course of the trial. OS is defined as the time from date of first SBRT dose to the date of death for any cause or is censored at the last known follow-up date. Exploratory outcomes include relationships between imaging and pathology (treatment response and resection margin status) and changes in markers of the innate and adaptive immune response before and during SBRT (cytological assessments and levels of interferon-related RNA).

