### Sample size considerations

Patient numbers will be determined by the primary endpoint of establishing the MTD, which will require a maximum of 24 evaluable patients. An evaluable patient for primary endpoint analysis is defined as one who has received at least one fraction of SBRT and experiences a DLT, or a patient who has received at least four fractions of SBRT and is assessed one month post-surgery (or assessed at similar time for DLT if no surgery). Patients not evaluable for primary endpoint will be replaced, but a patient who does not become evaluable for the primary endpoint may continue to be followed up for surgical outcome, PFS and OS as appropriate, unless consent is withdrawn.

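### The MTD can be declared, and recruitment stopped, on 0 DLTs in three patients, although the stated maximum of 24 evaluable patients already covers six at the selected level

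*Protocol article*

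**What the plan says.** Under Outcome measures and definitions, the primary endpoint is the MTD, "the highest level of SBRT at which no more than 1 of 6 patients or 0 of 3 patients experiences a DLT" during the DLT assessment period. The Abstract gives the same rule.

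Under Interventions, three clean patients also trigger escalation: "The dose level will be escalated if there is no DLT after the first three patients finish the DLT assessment period". The number of levels is given as "A maximum of 4 dose levels (including one de-escalated dose level) are expected to be needed to establish the MTD". On closing the trial: "Recruitment will stop once the MTD is identified". After a sixth patient enters a cohort, accrual pauses "until toxicity data is fully available for these six patients and/or a decision from the Trial Management Group (TMG) is made". That sentence describes a pause and sets no minimum cohort size.

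Under Sample size considerations, establishing the MTD is a task "which will require a maximum of 24 evaluable patients", and patients who are not evaluable are replaced. The Abstract puts the number differently: "Up to 24 patients will be recruited from up to 5 treating centres". Study design likewise gives 24 as the number to be recruited.

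**The concern.** No DLT in three patients is a common reason to move up a level, because the next cohort tests the decision. Here the same result can also be the end of the trial. If Level 3 shows 0 of 3, or if a level fails above one that was cleared on 0 of 3, the definition is met and recruitment stops with three patients at the declared dose.

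The MTD is the only primary result, and the Conclusion says that a phase II study follows once it is defined. Three patients without a DLT leave the DLT rate at that level very poorly known. The stated ceiling has room for a firmer basis, but the rule does not use it.

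Two wording points are linked. The number 24 is a recruitment cap in two places and an evaluable count with replacement in a third. The *and/or* in the pause sentence can be read as letting accrual resume on a decision before all six outcomes are known.

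**Working it through.** **Stated maximum.** The article gives no formula for 24. Four levels (−1, 1, 2, 3; Table 2) times a maximum cohort of six gives 4 × 6 = 24, which reproduces it.

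**Longest path**, taking outcomes as known at each decision:

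- As written: Levels 1, 2 and 3 at six each, 6 + 6 + 6 = 18. If Level 3 fails, Level 2 is already cleared and no one is added. If Level 1 fails, Level −1 follows: 6 + 6 = 12.
- Six required at the declared level: Level 1 at 0/3, Level 2 at 0/3, Level 3 fails on six, Levels 2 and 1 are each refilled by three and fail, Level −1 takes six. 3 + 3 + 6 + 3 + 3 + 6 = 24.

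**Precision.** Exact one-sided 95% upper limits for the DLT rate:

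- 0/3: 1 − 0.05^(1/3) = 63%
- 0/6: 1 − 0.05^(1/6) = 39%
- 1/6 (Clopper-Pearson): 58%

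**Chance that a level passes**, for true DLT rate p (assumed; the article states none). As written, with cohorts of three extended to six after one DLT: (1−p)³ + 3p(1−p)⁵. With six required: (1−p)⁶ + 6p(1−p)⁵.

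| p | As written | Six required |
|---|---|---|
| 0.10 | 0.729 + 0.177 = 0.91 | 0.89 |
| 0.20 | 0.512 + 0.197 = 0.71 | 0.66 |
| 0.33 | 0.301 + 0.134 = 0.43 | 0.36 |
| 0.40 | 0.216 + 0.093 = 0.31 | 0.23 |
| 0.50 | 0.125 + 0.047 = 0.17 | 0.11 |

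A cohort that fast accrual has already filled to six passes at the right-hand figure under either rule. The gap therefore shrinks as accrual speeds up.

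**How often the MTD rests on three patients.** The DLT window runs from the start of SBRT to one month after surgery: about 1 week of SBRT, 5-6 weeks to surgery and about 4 weeks after it, so 10-11 weeks (10.5 used). Patients were simulated as arriving at random, with allocation to the same level while data are pending, under several assumed sets of DLT rates:

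| Accrual | MTD on three patients | MTD on fewer than six |
|---|---|---|
| 1 per month | about 7% | about 15-18% |
| 0.5 per month | 22-24% | 42-46% |
| 0.25 per month | 42-44% | 61-67% |
| 1 per year | 58-64% | 68-76% |

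**Cost in patients.** If every cohort closes at three where the rules allow, full enumeration gives mean sizes of 10.2 as written and 12.7 with six required (assumed DLT rates 10/15/25/40% at Levels −1/1/2/3), a rise of 2.5. With rolling entry at fast accrual the rise is about 0.3.

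**Recruited versus evaluable.** Suppose 10% to 22% of patients are not evaluable. The 10% is purely illustrative. The 22% is the complement of the 78% who completed preoperative therapy and restaging in the 160-patient series cited in the Background. As written, 18 / 0.78 = 23.1, so a recruitment cap of 24 holds. With six required, the longest path needs 24 / 0.90 = 26.7 to 24 / 0.78 = 30.8, or 27 to 31 recruits.

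**The case against.** The strongest reply is that this is a rolling-six design, so a three-patient MTD is possible but not certain. While data are pending, new patients join the same level and cohorts tend to fill. This stands. A reader who treats the design as fixed cohorts of three would find three-patient MTDs in 60-76% of trials and infer that this is the usual ending. The allocation rules under Interventions do not support that inference at ordinary accrual. The Discussion does report one patient in the first year, which is the condition under which cohorts close at three, but eligibility has since been widened.

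Secondly, six patients are not decisive either. An accepted 1 of 6 has an upper limit of 58%, so the stricter rule does not exclude a majority DLT rate. Nor is at most 1 of 6 stricter in itself: at a 30% DLT rate it passes 42.0% of the time, against 34.3% for 0 of 3. The gain comes from adding three patients to a level already at 0 of 3, which cuts 34.3% to 26.9%. This limits the size of the point but does not remove it.

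Thirdly, a reader might take 24 against 18 as a sample size error, or as proof that refilling was intended. Neither follows: 24 is stated as a maximum, equals 4 × 6, and may simply be a cautious ceiling.

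A reader might also infer that few of three patients would reach surgery. The cited series point both ways (41% resected in one, 44 of 57 explored in another), so nothing here rests on it.

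The definition names only cohorts of three and six. This gap is narrow: 0 of 4 and 0 of 5 contain 0 of 3, and at 1 of 5 a sixth patient is the natural next step. Finally, the full protocol may hold a confirmation rule, but the article states a complete definition and a stopping rule, and together they permit the outcome described.

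**Conclusion.** The point holds as a worthwhile improvement to the design. The text permits the final MTD to be declared on 0 of 3, and the stated evaluable ceiling already covers six at the selected level.

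The benefit is moderate: at most 6 to 8 percentage points off the chance of passing a level with a true DLT rate of 33-50%, set against 2 to 5 points off the chance of passing one at 10-20%. Where no further DLT appears, the upper limit falls from 63% to 39%.

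The frequency figures rest on assumed DLT rates, random arrivals and a 10.5-week window. Accrual dominates them, from about 7% at one patient a month to about 60% at one a year.

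The conflict between recruited and evaluable numbers is real, but it bites mainly once six are required. The *and/or* is a genuine ambiguity.

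**What to change.** 1. Keep 0 of 3 as an escalation criterion only. Define the final MTD as the highest level with at most 1 DLT among six evaluable patients, and fill a level cleared on three to five patients to six before declaring it.
2. State 24 as the maximum number of evaluable patients, with replacements on top, and bring the Abstract and Study design into line with Sample size considerations.
3. Reword the pause after the sixth patient so that it is clear whether accrual may resume before all six toxicity outcomes are available.

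The cost is about 0.3-2.5 more patients on average (least with fast accrual), within 24 evaluable, plus the time to accrue them and up to one more DLT window. If 24 stayed a cap on recruitment, the longest paths could exceed it, so items 1 and 2 belong together.

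### The only example given for the discretionary DLT category, a fistula more than 30 days after surgery, falls almost wholly outside the period in which DLTs are counted

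*Protocol article*

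**What the plan says.** All references are to the protocol article.

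- **MTD and DLT period** (Outcome measures and definitions). The MTD is the highest level at which no more than 1 of 6, or 0 of 3, patients "experiences a DLT in the period from starting SBRT to one month post-surgery". For patients who are not operated on, the period ends "one month after the evaluation in week 3 post-SBRT if no surgery takes place".
- **Timing condition.** The DLT list that follows is limited to adverse events "seen in the DLT assessment period". This condition introduces the list and so applies to every item in it.
- **The item in question.** The last item covers other events that the TMG agrees are dose limiting and possibly related to SBRT. Its one illustration is a grade 3 or higher "gastrointestinal fistula >30 days after surgery".
- **Late toxicity** (same section). "Late toxicity is defined as any GI AE/other AE > grade 2 occurring between 1 month and 6 month post-surgery". This is a secondary outcome, and under Statistical analysis it is summarised descriptively.
- **Evaluability** (Sample size considerations). A patient without a DLT becomes evaluable on having "received at least four fractions of SBRT and is assessed one month post-surgery".
- **Dose assignment** (Interventions). Toxicity data count as pending for patients without a DLT who "are still in the DLT assessment period as defined in the outcome measure below". The dose is escalated if the first three patients finish that period with no DLT.

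**The concern.** The example of a DLT begins at about the point where the DLT period ends. An event has to satisfy both conditions to enter the count, and almost none can. The same event meets the definition of late toxicity, which plays no part in the written MTD rule.

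The MTD is the primary endpoint and rests on counts in groups of three or six, so a single patient can change the reading of a level. The wording also invites inconsistent rulings. Faced with a grade 3 fistula on day 35, one reader would follow the example and call it a DLT, and another would follow the period and call it late toxicity.

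**Working it through.** **The plan's own figure.** The stated maximum is 24 evaluable patients. With four dose levels and six patients per level, 4 × 6 = 24, so it reproduces. The point made here does not change it.

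**Step 1: compare the two timings.**

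| Quantity | Source | Value |
|---|---|---|
| End of DLT period, operated patients | Outcome measures and definitions | surgery + one month, 28 to 31 days depending on how a month is counted |
| End of DLT period, patients not operated on | same | one month after the week 3 evaluation; a post-surgical event cannot arise |
| Onset in the fistula example | same | later than day 30, so day 31 onwards |
| Late-toxicity window | same | 1 to 6 months after surgery, above grade 2 |

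Overlap in days = max(0, length of the month − 30).

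- Month of 28, 29 or 30 days: overlap 0.
- Month of 31 days: 31 − 30 = 1 day, namely day 31.

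A strict calendar month was counted from each of 1,461 consecutive possible surgery dates, starting on 1 April 2015. It has 31 days for 841 dates (841/1461 = 57.6%), 30 days for 500 (34.2%) and 28 or 29 days for 120 (8.2%). So even under the most generous reading, a little over half of surgery dates leave a single day of overlap and the rest leave none.

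**Step 2: look for a passage that rescues the event.** Evaluability is settled at the one-month assessment, and dose assignment uses the same period. Late toxicity takes over at one month. Nothing in the article extends the DLT period for this event or says that a later event alters a count already read.

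**Step 3: what one uncounted event does under the stated rule (0 of 3, or no more than 1 of 6).**

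| Count as written | Count with the event | Consequence |
|---|---|---|
| 1/6 | 2/6 | level passes as written, would fail otherwise |
| 0/3 | 1/3 | early pass lost; level can still pass at 1/6 |
| 0/6 | 1/6 | none; passes either way |

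**Step 4: illustration with assumed rates.** The article gives neither a DLT rate nor a fistula rate. Let p be the probability of a DLT inside the period and q the further probability of a late fistula, in a patient with no other DLT, that the TMG would judge dose limiting. Patients are taken as independent. With t = p + q:

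P(at most 1 of 6) = (1 − t)^6 + 6t(1 − t)^5

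For p = 0.15 and q = 0: 0.85^6 + 6 × 0.15 × 0.85^5 = 0.377 + 0.399 = 0.776.

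| p (assumed) | q = 0 (as written) | q = 0.05 | q = 0.10 | q = 0.15 |
|---|---|---|---|---|
| 0.10 | 0.886 | 0.776 | 0.655 | 0.534 |
| 0.15 | 0.776 | 0.655 | 0.534 | 0.420 |
| 0.20 | 0.655 | 0.534 | 0.420 | 0.319 |

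The table shows only how sensitive a six-patient rule is to one category of event. It does not estimate what would happen in this trial.

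**The case against.** Five points can be made on the other side.

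- **The fistula is not a stand-alone DLT.** It illustrates a category that depends on TMG agreement. The five specified items, and other events under the TMG category, can occur inside the period. This stands: the defect is confined to one example. But the category sits in the list governed by the timing condition, so TMG agreement does not bring the event into the count as written.
- **The event is not excluded in every case.** A reader might infer that it can never count, or that practically all such events are lost. The documents do not support so absolute a statement. A 31-day month leaves day 31, and how the month is counted and what tolerance the visit has are details that an article may leave to the full protocol. What is supported is that there is almost no usable overlap.
- **Escalation could still be halted.** A reader might infer that nothing could stop escalation after such an event. That goes too far. After the sixth patient, accrual is suspended until toxicity data are available and/or the TMG decides, and an independent committee reviews substantial decisions. Late events above grade 2 are recorded. These bodies could act on the event, but outside the DLT count that defines the MTD.
- **One event at 0/3 does not fail the level.** It is tempting to read 0/3 becoming 1/3 as a failed level. The rule also allows a pass at 1 of 6, so only the early pass is lost.
- **The phrase may mean a fistula that persists past day 30.** This does not help. Persistence beyond day 30 cannot be established before the period closes, apart from the same possible day.

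The article's condensed form is no answer either. Both conflicting timings are printed in it, within the primary endpoint definition.

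**Conclusion.** The point holds as an internal contradiction in the primary endpoint definition. The period in which DLTs are counted and the timing in the discretionary example overlap by at most one day, and by none if a month is 30 days or fewer. As written, a grade 3 or higher fistula after that time is late toxicity and does not enter the 0/3 or 1/6 count, even if the TMG judges it dose limiting.

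A single such event could make the difference between 1/6 and 2/6, or remove an early pass at 0/3. How often this would happen, and by how much it would move the MTD, cannot be said: the article gives no fistula rate, and the rates in the illustration are assumed. The conclusion about timing needs no assumption beyond a month of 28 to 31 days. It should be corrected because it lies in the definition that drives escalation and because correction is cheap.

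**What to change.** The sponsor and TMG should reconcile four places so that every event offered as a possible DLT can occur inside the period in which DLTs are counted:

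1. the end of the DLT period;
2. the timing in the fistula example;
3. the time point in the evaluable-patient definition;
4. the start of the late-toxicity window.

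They should also state how an event of this kind is treated for the MTD if it arises after the period has closed. Which timing holds, and what that treatment is, are for them to decide.

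The cost is a short amendment to these definitions. If the DLT period is the part that changes, cohort decisions come somewhat later. If only the example changes, the schedule of decisions is unaffected.
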